### Methods for additional analyses {20b}

No subgroup analyses will be done.

### Definition of analysis population relating to protocol non-adherence and methods to handle missing data {20c}

The intention-to-treat analysis will include all randomized subjects, ignoring non-compliance, protocol deviations, and withdrawal for any reason. Every effort will be made to obtain missing data, but missing data will be handled appropriately to minimize biases. We will explore the reasons for missing data and assess whether it is ignorable, or if it depends on other variables. Possible techniques to handle this could be imputation (e.g., mean imputation, multiple imputation).

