### Outcomes {12}

Primary outcome: Change in bone age from baseline to 12 months (difference in days).

Secondary outcomes:Breast development (puberty Z-scores [53])Anthropometry (height, weight, body mass index (BMI), waist-hip circumference, and ratio)Body composition (body fat percentage, lean mass, and gynoid/android fat distribution)Sex hormones (LH, FSH, estradiol, androgens, SHBG, AMH, and inhibin B)Insulin sensitivity (HOMA-IR) (calculated from fasting insulin and glucose)Age at menarche (electronic questionnaires)

Exploratory outcomes:Systolic blood pressure and resting heart rateMetabolic markers (i.e., cholesterol, triglyceride, leptin, and adiponectin)Fitness level (score)Daily physical activity level (time spent in different activity categories)Daily steps taken (only lifestyle intervention groups)Assessment of quality of life by online questionnaires (WHO-5 Well Being Score)

Safety parameters:Kidney and hepatic function tests (Na, K, urea, creatinine and ALAT, bilirubin)

Change in bone age after 12 months was chosen as the primary endpoint to evaluate the progression of puberty because both clinical and biochemical evaluations of pubertal stage can be challenging to accurately quantify. Automated determination of bone age will give us an objective measure of bone maturation which reflects growth velocity as an indicator of pubertal progression.

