## Methods: data collection, management and analysis

### Data collection and assessment of outcomes {18a}

See Fig. 2.

The primary outcome of this trial is defined as the difference in bone age (days) over 1 year determined by automatic bone age determination (BoneXpert, Visiana, Denmark [54]). An X-ray of the left hand and wrist will be performed at baseline, 6 months, and 12 months. At each center, the same version of the BoneXpert program will be employed for the determination of bone age (version 3; 2021). This method defines bone ages by Greulich & Pyle and Tanner-Whitehouse.

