### Statistical methods {20a}

The statistical analyses will be performed using the program R (R version 4.3.2, 2023 or later, The R Foundation for Statistical Computing). We will apply linear mixed-effects models to assess the effect of the intervention (± metformin, ± lifestyle) on the primary endpoint: changes in bone age (days). Furthermore, we will employ mixed-effects models to assess the effect of the intervention on the secondary outcome measures: breast development, sex hormones, insulin sensitivity, metabolic markers, fitness level, and body composition within and between treatment groups as well as age at menarche. Model assumptions for both linear and logistic mixed regression models will be assessed, including, where appropriate, checks for linearity, multicollinearity, random effects normality, and residual diagnostics.

Statistical analysis will be done separately for participants who complete follow-up (per-protocol) and the intention-to-treat population. Only participants that complete the intervention (have taken a minimum of 80% of the pills and participated in a minimum of 80% of the eventual allocated lifestyle intervention) will be part of the per-protocol population. Participants must in addition complete a minimum of the baseline visit and the follow-up visit at 12 months. A *P* value of <0.05 will be considered statistically significant. Estimates of treatment effects will be presented with 95% confidence intervals.

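### Mean imputation is named as a possible way to handle missing data, with outcomes not excluded; applied to 12-month bone age it would understate the standard error or shrink the estimated effect

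*Protocol article*

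**What the plan says.** The section on analysis populations and missing data {20c} sets the scope: "The intention-to-treat analysis will include all randomized subjects, ignoring non-compliance, protocol deviations, and withdrawal for any reason". It then states an aim, "missing data will be handled appropriately to minimize biases", and says that the reasons for missingness will be explored. It closes with the candidate methods: "Possible techniques to handle this could be imputation (e.g., mean imputation, multiple imputation". It does not say whether the mean would be taken within treatment group or over all girls, and it does not restrict the method to covariates.

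Three other places bear on the point:

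- Outcomes {12}: "Primary outcome: Change in bone age from baseline to 12 months (difference in days".
- Data collection {18a}: "An X-ray of the left hand and wrist will be performed at baseline, 6 months, and 12 months".
- Statistical methods {20a}: "We will apply linear mixed-effects models to assess the effect of the intervention (± metformin, ± lifestyle) on the primary endpoint: changes in bone age (days". The covariance structure is not given, nor is it stated whether the 6-month value enters the model.

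No expected dropout or missing rate is given anywhere in the article.

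**The concern.** Leaving the missing-data method to a statistical analysis plan would be no fault. Here, though, the protocol names a method, and that method is unsuitable for an outcome. A girl without a 12-month X-ray would receive a mean in place of her own value, and her baseline and 6-month bone ages would be ignored.

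If the mean is that of her treatment group, invented values are counted as observed ones: the sample looks larger and the spread smaller than they are. If it is the overall mean, the two groups are pulled together. Neither version corrects bias when missingness depends on other variables, which is a case {20c} itself raises. The named option therefore works against the section's own aim. At stake are the p-value and the effect estimate for the primary outcome.

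**Working it through.** **Inputs from the protocol article.** Metformin against placebo, 40 girls per group (Sample size {14}). Significance level: "value of <0.05 will be considered statistically significant" ({20a}); sidedness is not stated, so two-sided is taken. Design difference 11.9 − 11.4 = 0.5 years and SD 0.69 years, on age at menarche ({14}), which is 0.5/0.69 = 0.725 SD.

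**Assumed.** Missing fractions from 5% to 30%, equal in both groups, and values missing completely at random. *Group* means the metformin and placebo groups of 40.

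**Step 1: the plan's own figure.** n per group = 2 × (1.960 + 1.282)² × (0.69/0.5)² = 2 × 10.507 × 1.9044 ≈ 40.02. This rounds up to 41 (82 in total), against the stated 40 (80 in total). Power with 40 per group is 89.99%, so the stated 90% is reproduced.

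**Step 2: filling with the group mean, one change score per girl.** Let N = 40 be randomised and k observed per group. Filled values add nothing to the residual sum of squares but are counted in the degrees of freedom and the sample size. The ratio of true to reported standard error is

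r = √[ (2/k) / ( ((2k − 2)/(2N − 2)) × (2/N) ) ],

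and the actual type I error is 2 × P( t with 2k − 2 df > t₀.₉₇₅ with 2N − 2 df, divided by r ).

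At 20% missing, k = 32: r = √[0.0625 / ((62/78) × 0.05)] = √(0.0625/0.03974) = 1.254, and the type I error is 11.7%.

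| Missing | k | r | Type I error (formula) | Simulated, 40,000 trials |
|---|---|---|---|---|
| 5% | 38 | 1.053 | 6.3% | – |
| 10% | 36 | 1.113 | 7.8% | 7.7% |
| 15% | 34 | 1.179 | 9.6% | – |
| 20% | 32 | 1.254 | 11.7% | 11.9% |
| 25% | 30 | 1.339 | 14.2% | – |
| 30% | 28 | 1.436 | 17.1% | 16.8% |

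The rate passes 10%, twice nominal, at roughly 16% missing.

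**Step 3: does this depend on the model?** Group-mean filling at 20% missing:

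- Repeated measures at 6 and 12 months, unstructured covariance, 12-month contrast: 11.5-11.9%.
- Compound-symmetry or random-intercept model: 9.3-10.0%.
- Raw 12-month bone age filled in and the change then calculated: 8.3-10.2%, depending on the SDs assumed.

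The last two are about 1.7 to 2 times nominal.

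**Step 4: filling with the overall mean.** With a fraction f missing in each group, each group mean becomes (1 − f) × its observed mean + f × the overall mean, so the difference is multiplied by (1 − f). At f = 0.20 a true 0.50 becomes 0.40. The simulated means are 0.449 at 10%, 0.400 at 20% and 0.350 at 30%. At 20% the type I error is 4.9% and power 81%.

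**Step 5: no filling.** With 32 observed per group the type I error is 4.9%, the effect is unbiased (0.500) and power is 81%. A random-intercept mixed model fitted to the observed values held the type I error at 4.5-4.8% (400 runs per setting).

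**The case against.** The wording is tentative. Mean imputation stands in a list of examples next to multiple imputation, an acceptable method, and the order of such a list shows no preference. A reader might infer that the trial has committed to mean imputation, or that it has been ranked above multiple imputation; the text supports neither. An unseen analysis plan could settle the method before any data are examined, so the statement that reasons for missingness will first be explored does not by itself show a data-driven choice. All of this stands.

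A reader might also infer that the false-positive rate would more than double. The documents do not support that as a general statement. It needs roughly 16% or more missing, a rate they never give, and a single change score or an unstructured model, which they do not specify. Several provisions should keep missingness down: girls who withdraw from the intervention are invited to complete all assessments {17b}, contact is close {18b}, and data are monitored repeatedly for gaps {19}.

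Nor should overall-mean filling be read as a threat to validity of the test. It creates no excess false positives, and in the change-score comparison it loses no power against the observed data. Its fault is a biased estimate.

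Finally, {20c} speaks of missing data in general, and a repeated-measures model on all three X-rays is not stated in {20a}. The first point does not remove the concern: every randomised girl is to be analysed, so missing outcomes are within scope. The second is a reason to write the model down.

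**Conclusion.** The point holds as a should-fix. The protocol names, without excluding outcomes, a method that gives either a standard error that is too small or an effect that is too small when applied to the primary outcome.

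Under group-mean filling some inflation is present even at 5% missing. The size depends on the model and on a missing fraction that has to be assumed. Under overall-mean filling the harm is confined to the estimate. No variant examined made mean imputation of the outcome acceptable.

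The figures rest on two-sided testing and on equal missingness, completely at random, in both groups. The grade is not higher because the method is a non-binding example that a later document could drop.

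**What to change.** In {20c}, delete mean imputation as an option for outcomes. State that the primary intention-to-treat analysis is the linear mixed model of {20a}, fitted by likelihood to all observed bone ages at baseline, 6 and 12 months without single imputation. This uses partial follow-up under a missing-at-random assumption. Add multiple imputation as a sensitivity analysis, using treatment arm, baseline and 6-month bone age, and centre.

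The cost is one changed sentence and a little extra analysis. According to Trial status, recruitment is expected to run to February 2027, and {21b} rules out an interim analysis, so the change can be made before any outcome data are analysed.

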## Methods: monitoring

### Data monitoring committee {21a}

A study steering group consisting of the principal investigator and a Data Monitoring Committee (DMC) with an independent chair has been constituted with the purpose of assessing the progress and safety data of the LIFE-MET trial. The DMC will review the safety data every 6 months during the trial and report to the chief investigator and the sponsor. Based on its review, the DMC provides the sponsor with recommendations regarding trial modification, continuation, or termination. These reports will be included in the annual reports to the ethics committee. Further information can be found in CTIS.

### Interim analyses {21b}

No interim analysis will be performed. Statistical analysis will be done once the trial is completed.

### Harms {22}

Information on any potential adverse event or reaction (AE/AR) including its nature and severity will be collected at the local investigating site on clinical visits at 3 and 6 months and by telephone after 1 month of treatment. The principal investigator at each trial site will be responsible for performing supplemental measurements and/or evaluations as individually and medically indicated in case of adverse reactions. This could include physical examination and blood sampling, and if indicated, admittance to the local department of pediatrics. Participants will be followed up until resolution or stabilization, or until the event has been shown to be unrelated to the drug. Serious adverse events and serious adverse reactions should be reported to the sponsor immediately. AEs and ARs will be documented in the electronic case report form (eCRF) and in the “Summary of results” report that will be uploaded in CTIS within 1 year after completion of the trial. In addition, an annual safety report including a report on the safety of metformin will be submitted through CTIS.

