##### Lifestyle intervention

The lifestyle intervention will consist of:

Nutritional counseling for the parents in groups is performed online by a trained physician:The nutritional counseling will consist of an online session after the baseline visit where parents will be informed about the latest recommendations of a healthy diet for children from the Danish Food Agency, including guidance for healthier grocery shopping. In addition, information leaflets developed by the Danish Food Agency will be handed out or send to the parents.

An online training program twice a week for 6 months supervised by training experts with a background in exercise physiology:2.The online training will consist of both aerobic exercises and strength training. Training sessions will take place online twice a week and will consist of circuit training and active virtual reality gaming (AVRG) using the application FitXR, MetaQuest3. The participants will be able to interact and exercise with a private group with their coach and peers in the application FitXR.

Circuit training is a workout that involves rotating through various exercises targeting different parts of the body, such as squats, burpees, and jumping jacks. It involves endurance training, high-intensity aerobics, and exercises performed in a circuit, similar to high-intensity interval training. Sessions will begin with a warm-up, followed by a 5–20-min circuit training which increases throughout the intervention period following a schedule, and ending with 15–20 min of AVRG using FitXR. The AVRG will primarily consist of dancing or boxing sessions, as these were judged to be the most suitable sports in FitXR for children in this age group during a feasibility trial.

Participants in the lifestyle intervention group will receive a fitness watch (Garmin Vivofit Junior 3) with the purpose of displaying daily steps taken and motivating the girls to increase their daily physical activity level.

Fitness level (aerobic performance and explosive strength) will be evaluated for all participants prior to and after cessation of the intervention period using the following validated tests adapted to children: standing long jump, a 20-m sprint, and the YYIR1C (Yo-Yo Intermittent Recovery Level 1 for Children) [52]. In addition, the participants should wear an activity tracker for 1 week prior to and after cessation of the intervention period.

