#### Criteria for discontinuing or modifying allocated interventions {11b}

In case of gastrointestinal adverse effects of the medication, participants can be advised to divide the daily dose over two doses. In all participating girls, safety blood samples will be performed at baseline and at 3 and 6 months including renal (sodium (Na), potassium (K), creatinine, urea) and hepatic function tests (alanine transaminase (ALAT), bilirubin). A progressive increase of creatinine, urea, ALAT, or potassium levels will be a reason for discontinuing the medication. Persistent gastrointestinal adverse effects (vomiting, nausea, abdominal pain) and a persistent skin rash are also reasons for discontinuation of the medication.

Participants will be instructed to pause treatment with metformin or placebo in case of moderate or severe dehydration/repeated vomiting, severe infection requiring hospitalization, or in case of an operation requiring general, spinal, or epidural anesthesia. Participants will also be instructed to inform health personnel of their participation in the trial in case of hospitalization. In case of pausing treatment, participants are asked to inform the local PI.

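### Adverse-event follow-up may end once an event is shown to be unrelated to the drug, so a non-serious injury from the randomised exercise programme can be closed before its outcome is known

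*Protocol article*

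**What the plan says.** Harms {22} sets the follow-up rule: "Participants will be followed up until resolution or stabilization, or until the event has been shown to be unrelated to the drug". The lifestyle programme is not mentioned in that sentence or elsewhere in the section.

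The same section casts a wide net for collection and reporting. On collection: "Information on any potential adverse event or reaction (AE/AR) including its nature and severity will be collected at the local investigating site", with contacts by telephone at 1 month and at the 3- and 6-month visits. Both adverse events and adverse reactions are entered in the eCRF and in the results report. On serious events: "Serious adverse events and serious adverse reactions should be reported to the sponsor immediately". Neither provision depends on whether the drug was the cause.

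Trial design {8} and Interventions for each group {11a} describe four arms of 20 girls, two of which receive the lifestyle intervention. Under Lifestyle intervention, its exercise part is described as "An online training program twice a week for 6 months supervised by training experts". It combines circuit training, which the article likens to high-intensity interval training, with virtual-reality sessions that are mainly dancing or boxing.

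**The concern.** A rule that ends follow-up on causal grounds should test causality against everything the trial assigns. Here it tests one of two randomised interventions. A sprain from a training session is a clear example: a blinded site can conclude without unblinding that the tablets did not cause it. The third ending point is then met while the injury is still open, although another trial intervention caused it.

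What is at stake is knowledge of how such injuries end and how long they last, in children. Objectives {7} includes the lifestyle effect among the secondary objectives. The Discussion calls evidence on online virtual-reality training in children sparse and wants more experience before wider use. How harms of that training turn out is part of that experience.

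**Working it through.** No sample size, power or error rate enters this point, and the plan gives no figure to reproduce. The check sets the sections side by side.

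**1. Who is exposed to the second intervention.** From Trial design {8}: metformin + lifestyle 20, placebo + lifestyle 20.
- Girls allocated to the programme: 20 + 20 = 40 of 80, or 40/80 = 50%.
- Of these, 20 take placebo, so none of their events can be caused by metformin.

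**2. What the rule does with a training injury.** There are three ending points:
- Resolution: nothing is lost.
- Stabilisation: nothing is lost that the plan meant to keep.
- Shown to be unrelated to the drug: an injury from a training session can meet this at once, before either of the others.

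The loss is therefore confined to injuries that are still open when they are judged unrelated to the tablets and that the site chooses to close then. The rule permits closure and does not require it.

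**3. Whether another section closes the gap.** Outcomes {12} lists kidney and liver function tests as the safety parameters. Harms {22} names adverse-event collection at 1, 3 and 6 months. The programme also ends at 6 months, so for an injury still open at that point the follow-up rule is what the article offers for learning its outcome. No section shown states a follow-up or causality rule for the lifestyle programme.

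**4. What stays intact.**

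| Item | Affected? | Source |
|---|---|---|
| Occurrence, nature and severity of the event | No | Harms {22}, collection of any event |
| Entry in the eCRF and results report | No | Harms {22}, events as well as reactions |
| Immediate reporting of serious events | No | Harms {22}, no condition on cause |
| Primary analysis of bone age | No | Statistical methods {20a} |
| Outcome and duration of a non-serious programme-related injury | Possibly | Harms {22}, third ending point |

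**The case against.** The strongest reply is that the sentence is being read out of context. Just before it, the section assigns the site investigator "supplemental measurements and/or evaluations as individually and medically indicated in case of adverse reactions". On that view the follow-up sentence completes the work-up of a suspected drug reaction: follow it until it settles or proves not to be a reaction. Follow-up of exercise injuries would then simply be unstated, and a condensed article may leave such detail to the full protocol, which Reproducible research {31c} says is available in CTIS.

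This has some force, but the sentence speaks of the event, not the reaction, and its third ending point only makes sense while causality is still open. As printed it is a stated rule that a site could apply to any event. The full protocol may be worded more broadly, but it is not shown.

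The second reply is that an injured girl does not leave observation, and this largely stands. Clinical variables are collected at 3, 6 and 12 months. Under {17b}, a girl who withdraws from the intervention is invited to continue with visits and assessments. The data monitoring committee reviews safety data every six months. The annual safety report includes metformin without being limited to it. These provisions limit the consequence, but none of them requires that a closed injury be followed to its outcome.

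**Conclusion.** The point holds as a narrow one. The rule in Harms {22} does not match the two-intervention design, and it allows the outcome and duration of non-serious programme-related injuries to go unrecorded among the 40 girls allocated to the programme. This rests on a literal reading of the follow-up sentence and on the article alone. It is a cheap improvement to participant safety and to the completeness of harm outcomes, not a threat to the trial's main conclusion.

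A reader might infer more, and the documents do not support it:

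- *That exercise injuries are dropped.* They can be closed early; nothing requires it, and they are still collected and recorded.
- *That the lifestyle versus no-lifestyle harm comparison is biased towards safety.* Events, with their nature and severity, are collected in all four arms, so event counts are unaffected. Only outcome and duration may be incomplete.
- *That the number of affected events can be estimated.* The documents give no injury rate, and injuries that resolve or stabilise first never reach the third ending point.
- *That {11b} is at fault because its heading speaks of allocated interventions while its criteria, such as those that "are also reasons for discontinuation of the medication", concern the tablets only.* The heading is a SPIRIT item label, and the absence of criteria for the exercise programme from a condensed article is an omission, not a contradiction.

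**What to change.** In the follow-up sentence of Harms {22}, replace the reference to the drug so that the third ending point reads: *unrelated to either trial intervention (tablets or lifestyle programme)*. Have the site judge relatedness to each intervention when it records an event. If the full protocol already says this, the article's sentence should be brought into line with it.

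The cost is one phrase, one more causality judgement per event, and a few events followed a little longer. Blinding, sample size and the analysis do not change. Trial status gives February 2027 as the expected end of recruitment, so an early correction would cover girls still to be enrolled.
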